### Data analysis

TEDDI is a non-randomized feasibility study and for this mainly descriptive statistics will be applied. The patient cohort will be described by demographic data, histological diagnosis, stage, age, and gender. For each patient, target volumes (GTV, CTV, and PTV) and OARs volumes of the two planning CT scans will be compared. Maximum and mean doses as well as the volumes exposed to 5/10/20/30 Gy will be compared. The Wilcoxon signed rank test for paired data will be used for statistical testing.

The dosimetric parameters are surrogate markers for the potential clinical benefit with DIBH compared to FB RT plans as an observed, significant reduction in treatment-induced late effects would require several decades of follow-up in a patient cohort consisting of several hundreds of patients. The expected clinical implications will, however, be estimated by applying normal tissue complication probability-models derived from clinical case-control and cohort studies.

Patient compliance is defined as patient comfort and DIBH reproducibility. Hence compliance will be assessed using both qualitative and quantitative measures. Patient comfort will be assessed through daily questionnaires based on a 5-point Likert scale. Tumor position will be used to evaluate the ability of patients to maintain the breath-hold during the whole course of treatment and to investigate the possibility that patients might get weaker and/or more tired and thus unable to perform a stable DIBH as the treatment course progresses. This will be done using the respiratory motion management system.

The accuracy of the treatment delivery will be evaluated based on daily imaging. If the target is not visible, the sternum (mediastinal tumors) or the diaphragm (abdominal tumors) will be used as a surrogate structure. If the target position appears reproducible within 5 mm, the patient will be deemed compliant. In addition to the daily online positioning at the treatment machine before each fraction, the reproducibility of the target position will be assessed retrospectively by a medical physicist on a weekly basis.

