## Methods/Design

### Aims and hypothesis

TEDDI aims toEstimate the dosimetric benefit of RT using DIBH compared to free breathing (FB) in pediatric patients.

*Hypothesis 1: For more than 75% of patients, treatment in DIBH will be dosimetrically superior to treatment in FB.*

2)Establish the compliance of DIBH in pediatric patients.

*Hypothesis 2: Over 90% of pediatric patients from the age of five years will be able to perform stable, reproducible, and comfortable DIBHs (of 20 seconds) through their course of RT.*

3)Determine if DIBH is an accurate and reproducible strategy for pediatric patients.

*Hypothesis 3: The tumor position will be reproducible from day to day, as well as from DIBH to DIBH. Variations in tumor position will be less than 5 mm over the whole treatment course.*

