**Fig. 1 Fig1:**
[figure not shown]
A six year old healthy volunteer perform deep inspiration breath-hold using the Real-time Position Management system from Varian Medical Systems (Palo Alto, USA). The screen provides a visual feed-back and helps guide the volunteer’s  respiration. Notice how the immobilization device does not support the volunteer sufficiently; if the volunteer was to receive radiotherapy a custom made fixation device should be constructed

The patient is deemed compliant if he/she successfully completes three sequential DIBHs of 20 s each during the 20 min training session.

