### Safety

Procedures for patient safety and quality assurance during RT will be adhered to, irrespective of treatment in DIBH or FB. Patient compliance will be assessed through a questionnaire after each delivered RT fraction. Patients that initially or at any point during treatment cannot comply with the DIBH procedure will be treated in FB. A change from DIBH to FB must not cause a delay in the patient’s treatment course.

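### The 5 mm position rule on its own makes a child compliant, although the plan defines compliance as comfort plus reproducibility and Hypothesis 2 asks for more still

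*Protocol article*

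**What the plan says.** Hypothesis 2 (Aims and hypothesis) is: "Over 90% of pediatric patients from the age of five years will be able to perform stable, reproducible, and comfortable DIBHs". It specifies holds of 20 seconds and sets the period as "through their course of RT".

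The Data analysis section gives a composite definition: "Patient compliance is defined as patient comfort and DIBH reproducibility". It adds that both qualitative and quantitative measures will be used, with comfort taken from daily questionnaires on a 5-point scale. The next paragraph, on accuracy of delivery, states a rule on position alone: "If the target position appears reproducible within 5 mm, the patient will be deemed compliant".

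The Safety section covers children who fail during treatment: "Patients that initially or at any point during treatment cannot comply with the DIBH procedure will be treated in FB". It does not say how such a child is classified for Hypothesis 2, and neither does the Data analysis section.

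**The concern.** The two Data analysis statements do not select the same children. Under the composite a child must be comfortable and reproducible; under the later rule being reproducible is enough. That rule also gives no hold duration and no period, so it does not require 20-second holds or success to the end of the course.

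The gap matters most for a child moved to free breathing. Breath-hold position data end at the switch. If the fractions before it were within 5 mm, the rule as worded can still label the child compliant, although the child did not perform breath-holds through the course.

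Compliance is one of three stated aims of this feasibility study, and the target is a proportion in about 25 children. A few classifications decide whether it is reported as met.

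**Working it through.** **Step 1. The requirements side by side.**

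| Requirement | Hypothesis 2 | Composite definition | 5 mm rule |
|---|---|---|---|
| Reproducible | yes | yes | yes (5 mm) |
| Comfortable | yes | yes | no |
| 20-second holds | yes | not stated | no |
| Through the whole course | yes | not stated | not stated |

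The 5 mm rule is the only one of the three with a numerical cut-off for calling a treated child compliant, and it covers one of the four requirements.

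**Step 2. The plan's own figure.** The only computed figure, power 0.85 with 22 patients, concerns mean heart dose and so Hypothesis 1. It reproduces: a difference of 25% × 4 Gy = 1 Gy, SD 1.5 Gy taken as that of the paired difference, and a two-sided paired t-test at 0.05 give 0.846. It has no bearing on Hypothesis 2, for which the article states only the threshold.

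**Step 3. How many failures decide Hypothesis 2.** Planned enrolment is 25 (Patients section). Over 90% means more than 0.90 × 25 = 22.5, so at least 23 successes. The number of switches is assumed, since the article gives none. Suppose all 25 start in breath-hold, k switch for non-compliance, and the rest meet every component. The rate is then (25 − k)/25. The exact (Clopper-Pearson) 95% limits for x successes in n are the 0.025 quantile of Beta(x, n − x + 1) and the 0.975 quantile of Beta(x + 1, n − x).

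| Switches k | Switch = failure | Exact 95% CI | Over 90%? |
|---|---|---|---|
| 1 | 24/25 = 96% | 79.6% to 99.9% | yes |
| 2 | 23/25 = 92% | 74.0% to 99.0% | yes |
| 3 | 22/25 = 88% | 68.8% to 97.5% | no |
| 4 | 21/25 = 84% | 63.9% to 95.5% | no |
| 5 | 20/25 = 80% | 59.3% to 93.2% | no |

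**Step 4. The same children counted otherwise, k = 3.**
- Switchers drop out of the denominator: 22/22 = 100%.
- Switchers were within 5 mm before the switch and are called compliant by the 5 mm rule: 25/25 = 100%.
- Switchers count as failures: 22/25 = 88%.

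**Step 5. A smaller denominator.** Not every enrolled child need start radiotherapy in breath-hold, because inclusion requires only a possible need for radiotherapy and some plans may favour free breathing. With 22 starting, 20/22 = 90.9% passes and 19/22 = 86.4% (65.1% to 97.1%) does not, so three failures again decide. With 20 starting, two suffice: 18/20 = 90%, which is not over 90%.

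**The case against.** The strongest defence is that the 5 mm sentence stands in the paragraph on delivery accuracy and can be read as the cut-off for the reproducibility half of the composite defined one paragraph earlier. Hypothesis 2 also sets the period as the whole course, so on a plain reading a child moved to free breathing for non-compliance has failed. Both readings are sensible, and the fix adopts them. But the sentence does not say this: it makes the patient, not a component, compliant on position alone.

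A reader might infer more than the article supports.

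- **That compliance has several conflicting definitions.** In the Training session section, "The patient is deemed compliant if he/she successfully completes three sequential DIBHs" describes a gate at that stage and matches the inclusion criterion. In the Safety section, "Patient compliance will be assessed through a questionnaire after each delivered RT fraction" describes the instrument for the comfort half of the composite. Neither competes with the definition for the treatment course. The conflict is between the composite and the 5 mm rule.
- **That Hypotheses 2 and 3 can both be met by losing the failures.** The article nowhere excludes switchers or restricts an analysis to compliant patients. Hypothesis 3 is a bound on position variation with no proportion of patients attached, so a switch is not a countable failure there. A switch for discomfort also says nothing about position.
- **That the 5 mm bound becomes harder to meet in longer courses.** Any figure for this depends on an assumed positional SD, which the article does not give.

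A condensed article may leave the analysis set and the comfort cut-off to a fuller document, so their absence alone is no fault. The contradiction is different, because it lies in the text as it stands.

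**Conclusion.** The point holds in this form: the Data analysis section contradicts itself, and its 5 mm rule is weaker than both its own composite definition and Hypothesis 2. A child in discomfort, one holding for less than 20 seconds, or one within 5 mm only before a switch can be counted as compliant.

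The effect can be decisive for the point estimate. With 25 starting in breath-hold and 3 switching, the result is 88% or 100% depending on how those three are classified. This rests on assumed counts and on the remaining children meeting every component. It does not show a significant shortfall: every interval in the table includes 90%, and the study is mainly descriptive with no stated test against 90%. Loss of failures from the denominator is possible under the present wording, not planned by it.

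For Hypothesis 3 the point is limited to reporting. Breath-hold positions end at a switch, so the result needs the number of switches beside it. The safety rule that moves children to free breathing is not in question.

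**What to change.** 1. State that 5 mm is the cut-off for the reproducibility component only.
2. Define Hypothesis 2 success for each patient as all its stated components together: stable, reproducible and comfortable 20-second holds through the course. The sponsor should set the comfort cut-off on the 5-point scale in advance.
3. Use all patients who start radiotherapy in breath-hold as the denominator, and count a switch to free breathing for non-compliance as a Hypothesis 2 failure. Children who cannot comply before the first fraction fall outside this denominator, so give their number beside the rate.
4. For Hypothesis 3, report position variation over all breath-hold fractions of all patients who start in breath-hold. Include fractions before a switch, do not restrict to patients deemed compliant, and give the number of switches alongside.

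The cost is protocol wording. The questionnaires, the breath-hold monitoring and the daily imaging are already planned, so no new data are needed. The downside is a compliance rate that may look less favourable.

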### Sample size

Sample size is calculated based on a presumed mean heart radiation dose of 4 Gy in FB and a 25% reduction in mean heart dose with treatment in DIBH, with a standard deviation of 1.5 Gy across the patient group [16]. Recruiting 22 patients would lead to a power of 0.85 to detect this dosimetric difference. The Type 1 error probability is set at 0.05.

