### Patients

25 consecutive, pediatric cancer patients will be included.

Inclusion criteria:Age 5–17 years.Patients with a tumor in the mediastinum or upper abdomen with the possible need for RT according to current treatment guidelines, irrespective of cancer diagnosis.The ability to perform three sequential DIBHs of 20 s each during a training session.Written informed consent from parent(s) or legal guardian(s).

Exclusion criteriaAge < 5 years or > 17 years at time of diagnosis.The need for sedation during RT.CNS tumor or pelvic localization.Unable to understand DIBH coaching information directly or through interpretation.

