## Discussion

The dosimetric benefit from RT in DIBH has been well documented in the adult setting [14–17], however respiratory motion management is not routinely used in the pediatric setting.

TEDDI is the first formalized study to introduce RT delivery in DIBH for pediatric patients.

Prior to clinical implementation of TEDDI, a pilot study was conducted at Rigshospitalet in order to investigate whether children from the age of five are able to perform stable and reproducible DIBHs using the RPM system. To assess the patient compliance qualitatively, the participating children and families completed a questionnaire after the DIBH training session. The questionnaire evaluated the child’s comfort with the pre-training information and the DIBH coaching. Based on experiences gained from this pilot study a standard operating procedure for RT delivery in DIBH for pediatric patients has been developed.

Two prior studies have described the experience with DIBH in pediatric patients [19, 20]. Both studies used a spirometry-assisted breath-hold technique. Claude et al. [19] concluded that only older children are able to comply and understand the technique, and it increases the estimated daily treatment time at the linac. Spirometry-assisted DIBH has in adults been reported less comfortable than the optical surface tracking DIBH approach [26], employed in TEDDI. Our DIBH-method is performed as a non-invasive procedure and constitutes a very gentle treatment expected to cause a minimal inconvenience to this fragile patient population. When treating very young children, however, prolonged treatment time at the linac might be unavoidable.

Recently Huijskens et al. investigated the respiratory-induced motion of the diaphragm and the intra- and interfractional variability in children during image-guided RT [27]. They found a large range of the diaphragm amplitude motion, mean 10.7 mm (range 4.1–17.4 mm), with the intrafractional variability being the largest. Because of the substantial patient variability they concluded that a 4DCT in children should be performed to quantify the individual respiratory motion in order to define individual safety margins. TEDDI will clarify whether RT in DIBH can reduce this variability, potentially allowing for smaller margins and, thus, a reduced dose to the OARs.

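### The stated power of 0.85 at 22 patients holds only for a paired t-test with 1.5 Gy as the SD of the within-patient difference; for the planned Wilcoxon test it is about 0.82

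*Protocol article*

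**What the plan says.** The Sample size section of the protocol article starts from a "presumed mean heart radiation dose of 4 Gy in FB". The effect to be detected is given as "a 25% reduction in mean heart dose with treatment in DIBH". On variability the section offers only the phrase "with a standard deviation of 1.5 Gy across the patient group", and it refers to a cited earlier study. It concludes: "Recruiting 22 patients would lead to a power of 0.85 to detect this dosimetric difference". Alpha is 0.05. The section does not name the test, say whether it is one- or two-sided, give a correlation between the two plans, or say whether the SD belongs to the dose or to the paired difference.

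The Data analysis section does name the test: "The Wilcoxon signed rank test for paired data will be used for statistical testing". Under Treatment planning, each patient has a planning scan and a plan in both FB and DIBH, so the comparison is within patients. The Patients section plans 25 inclusions, three more than the 22 in the power statement. Eligibility requires only that radiotherapy may be needed, so an included patient does not necessarily contribute a pair of plans.

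**The concern.** The power of a paired comparison depends on the SD of the within-patient difference. An SD described as lying across the patient group can mean the spread of dose between patients or the spread of the individual reductions. The two coincide only under a particular correlation between the FB and DIBH doses, and the section gives none. The quoted power also appears to belong to a t-test, while the planned test is rank-based. This is the only sizing statement in the document, so a reader needs to know which SD and which test the 0.85 describes before judging whether 22 pairs are enough.

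**Working it through.** **Inputs from the protocol.** Mean heart dose in FB 4 Gy; reduction 25%; SD 1.5 Gy; n = 22; alpha 0.05; stated power 0.85 (all Sample size). Test: Wilcoxon signed rank (Data analysis). Planned inclusions: 25 (Patients).

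**Step 1: reproduce the stated figure.** Difference to detect = 0.25 × 4 = 1.0 Gy. Take 1.5 Gy as the SD of the paired difference. The noncentrality of the paired t-test is (1.0 / 1.5) × √22 = 3.127 on 21 degrees of freedom, and the two-sided 5% critical value is 2.080. Power from the noncentral t distribution is 0.846, which rounds to 0.85.

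Other calculations with the same inputs do not match:

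| Calculation at n = 22 | Power |
|---|---|
| Paired t, two-sided | 0.846 |
| Paired, normal approximation, two-sided | 0.878 |
| Paired t, one-sided | 0.916 |
| Two independent groups of 22, t-test, two-sided | 0.58 |

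So the stated power was most likely obtained from a two-sided paired t-test with 1.5 Gy as the SD of the difference.

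**Step 2: power of the planned test.** Keep 1.5 Gy as the SD of the difference and assume normally distributed differences. Power of the two-sided Wilcoxon signed rank test with its exact critical value was obtained by simulation (200,000 data sets per row). The t-test is alongside for comparison:

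| Complete pairs | Wilcoxon | Paired t |
|---|---|---|
| 22 | 0.82 | 0.846 |
| 23 | 0.85 (0.845) | 0.863 |
| 25 | 0.88 | 0.892 |

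The Wilcoxon test costs about 2 points at 22 pairs. One more pair recovers the stated power to two decimals.

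**Step 3: the other reading of the SD.** Suppose 1.5 Gy is the between-patient SD of heart dose, equal in FB and DIBH. Then the SD of the difference is 1.5 × √(2(1 − ρ)), where ρ is the FB-DIBH correlation. The documents give no ρ, so the values below are assumptions. Two-sided paired t-test, 22 pairs:

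| Assumed ρ | SD of difference (Gy) | Power |
|---|---|---|
| 0 | 2.12 | 0.56 |
| 0.3 | 1.77 | 0.71 |
| 0.5 | 1.50 | 0.85 |
| 0.7 | 1.16 | 0.97 |
| 0.8 | 0.95 | 0.997 |

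The two readings agree only at ρ = 0.5, where √(2 × 0.5) = 1.

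**The case against.** The strongest reply is that the number is right. The design is paired, the SD phrase directly follows the reduction, and the SD of individual reductions is itself a spread across patients. On that reading 0.85 follows, and nothing shows that 1.5 Gy was misused. This stands: the wording is ambiguous, and a reader who infers that the stated power is an arithmetic error goes further than the text allows. What the cited study's 1.5 Gy refers to cannot be checked from the document.

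It is also fair that the low powers in Step 3 need a low correlation. Two plans for the same patient, made with similar objectives, may well correlate above 0.5, and then 22 pairs would be conservative even if 1.5 Gy is the between-patient SD. The range shows what the wording leaves open; it is not evidence that the study is underpowered.

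The Wilcoxon loss is small, and 25 complete pairs more than cover it. That stands too, provided all 25 have both plans. It does not make the sentence about 22 patients correct for the planned test.

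Finally, the study is a feasibility study with mainly descriptive statistics, and an article may leave detail to the full protocol. But the article chose to state this calculation, so its key input and its test should be identifiable.

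A reader might also infer that power is much lower because the cohort mixes mediastinal and upper abdominal tumors ("Patients with a tumor in the mediastinum or upper abdomen with the possible need for RT according to current treatment guidelines") while the inputs come from a study in adults. The documents give no abdominal share and no heart dose for those patients, so this effect cannot be quantified and is not part of the point.

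**Conclusion.** The point holds as a matter of labelling, with a small numerical consequence. The claim that 22 patients "would lead to a power of 0.85" is correct for a two-sided paired t-test if 1.5 Gy is the SD of the within-patient difference. The section says neither, and for the test actually planned the figure is about 0.82. The Wilcoxon figures assume normal differences and complete pairs; the correlation range assumes equal SDs in FB and DIBH. It would be wrong to conclude that the study is underpowered or that a null result could not be interpreted: the paired data will supply their own SD and interval, and 25 complete pairs give about 0.88.

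**What to change.** In the Sample size section:

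- State that 1.5 Gy is the SD of the within-patient FB-DIBH difference in mean heart dose, if that is what the cited study supports. Otherwise give the between-patient SD with the assumed FB-DIBH correlation and recompute the power.
- Name the Wilcoxon signed rank test and the two-sided level. If 1.5 Gy is the SD of the difference, restate the power as about 0.82 at 22 complete pairs and about 0.88 if all 25 planned patients have both plans, assuming normal differences.

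This means rewriting about two sentences. The only cost is a slightly less favourable figure at 22 pairs. Recruitment, the analysis population and the planned test need no change.

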## Discussion

The dosimetric benefit from RT in DIBH has been well documented in the adult setting [14–17], however respiratory motion management is not routinely used in the pediatric setting.

TEDDI is the first formalized study to introduce RT delivery in DIBH for pediatric patients.

Prior to clinical implementation of TEDDI, a pilot study was conducted at Rigshospitalet in order to investigate whether children from the age of five are able to perform stable and reproducible DIBHs using the RPM system. To assess the patient compliance qualitatively, the participating children and families completed a questionnaire after the DIBH training session. The questionnaire evaluated the child’s comfort with the pre-training information and the DIBH coaching. Based on experiences gained from this pilot study a standard operating procedure for RT delivery in DIBH for pediatric patients has been developed.

Two prior studies have described the experience with DIBH in pediatric patients [19, 20]. Both studies used a spirometry-assisted breath-hold technique. Claude et al. [19] concluded that only older children are able to comply and understand the technique, and it increases the estimated daily treatment time at the linac. Spirometry-assisted DIBH has in adults been reported less comfortable than the optical surface tracking DIBH approach [26], employed in TEDDI. Our DIBH-method is performed as a non-invasive procedure and constitutes a very gentle treatment expected to cause a minimal inconvenience to this fragile patient population. When treating very young children, however, prolonged treatment time at the linac might be unavoidable.

Recently Huijskens et al. investigated the respiratory-induced motion of the diaphragm and the intra- and interfractional variability in children during image-guided RT [27]. They found a large range of the diaphragm amplitude motion, mean 10.7 mm (range 4.1–17.4 mm), with the intrafractional variability being the largest. Because of the substantial patient variability they concluded that a 4DCT in children should be performed to quantify the individual respiratory motion in order to define individual safety margins. TEDDI will clarify whether RT in DIBH can reduce this variability, potentially allowing for smaller margins and, thus, a reduced dose to the OARs.

DIBH seems to be compatible with proton therapy, however, data and availability is still limited. The experience gained from TEDDI will be directly transferable to proton treatment facilities. Also, DIBH holds the potential for synergistic combinations with other new RT principles, e.g. dose painting with a boost to radio-resistant areas of the tumor, as this technique requires that tumor motion is minimal in order to deliver the radiation dose correctly.

In conclusion, RT in DIBH is a promising technique in a pediatric setting, which could have a dramatic impact on the risk of late effects following RT for childhood cancer, improving subsequent quality of life, morbidity, and - ultimately - mortality.

